### Data collection method

In order to evaluate the effectiveness of this program, data is collected from participants through an online survey. Participants are invited to complete online questionnaires that assess their family empowerment, caregiver burden, self-reported capability to use social resources, self-compassion, and quality of life. A survey request email is sent to the participants regarding the online survey at the times described below, and one or more reminders are sent to those who do not respond. Participants are requested to cooperate in the survey regardless of their program attendance. For example, even if a participant does not attend any sessions, they are asked to complete the survey.

The online survey is conducted at the following three time points. After the participants apply for the program and are allocated to either the early or delayed group, they are notified of their attendance month (from July to December). At the time, participants are not informed if they are in the early or delayed group; they are simply notified of their attendance month to prevent response bias based on the participant’s impression of their allocated group. Thereafter, the initial evaluation (Time 1 [T1]) is conducted before the early group starts the first session. For the early group, this corresponded roughly to a week before attending the program. The post-intervention evaluation (Time 2 [T2]) is conducted immediately (within 1 week) after the early group completed all four sessions in the program (4 weeks). The follow-up evaluation (Time 3 [T3]) is conducted 4 weeks after the post-intervention evaluation. The timings are the same for the delayed group; however, it begins the program precisely 4 weeks after the early group does. That is, the delayed group completes the evaluation for T1 roughly 5 weeks before attending the program, T2 immediately before attending the program, and T3 immediately after completing the course.

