### Data analysis

For the assessment of feasibility, which is the primary outcome of this study, descriptive statistics will be used to assess the feasibility outcomes, such as the recruitment and retention rate of participants across the intervention. Intervention acceptability will be assessed through analysis of the level of satisfaction, opinions, and free responses related to the program described and listed.

This program is designed such that attending a total of four sessions enables participants to sequentially review their family situation including the relationships within their families and their social resources, their own, and their family members’ lives and to visualize their family relationships, burden, and the use of services. Specifically, after attending the program, participants are expected to have an improved sense of family empowerment immediately, including establishing and practicing specific and feasible plans. Therefore, to verify the effectiveness of the program, the primary outcome measure is the total FES score at T2. The secondary outcomes are to verify improvement in the levels of family empowerment (FES subscale score at T2), whether aspects directly addressed in the program had improved (caregiver burden, self-reported capability to use social resources, self-compassion at T2), and whether they had a comprehensive effect (health-related QOL at T2). Furthermore, whether any interventional effect observed at T2 is sustained (each outcome score at T3 for the early group), and whether any interventional effect observed in the early group is reproduced (each outcome score at T3 for the delayed group) is verified. The statistical analysis plan is described as follows:

The responses, wherein the outcome scores can be calculated as valid responses, are used. ITT analysis is performed to manage data from participants who deviate from the study protocol by not attending the program at the designated times as the original allocation group. First, descriptive statistics are calculated for the background attributes and outcome scores of the participants (both the participant and the child) at T1. The interval scale is used to calculate the mean and standard deviation; ordinal and nominal scales are used to calculate the frequency and proportion, and intergroup comparison is performed using Welch’s *t* test, the Mann-Whitney *U* test, and Fisher’s exact probability test.

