There is a possibility of participants dropping out between T1 and T2 and between T2 and T3. Therefore, we compare the background attributes and outcome scores at T1 between the primary outcomes “total FES score of valid respondents at T2” and “non-respondents at T2 (but are valid respondents at T1)” to examine and discuss the effect caused by participants dropping out. In addition, an intergroup comparison of background attributes and outcome scores at T1 is conducted for a population of only the “total FES score of valid respondents at T2.” If group differences that may create significant bias or biased dropouts are observed in the analysis to date, we aim to consider adding those variables as covariates in subsequent analyses.

The primary analysis is an intergroup comparison using analysis of covariance with the total FES score at T1 as the covariate, and the total FES score at T2 as the dependent variable. In case of a significant interaction between the independent variable (group: early group or delayed group) and the covariate (total FES score at T1), an intergroup comparison is conducted using ANOVA without considering the scores at T1. The level of statistical significance is set as 5%. Interim analysis is not performed. Subgroup analysis is conducted for children with severe disabilities, children with disabilities who need constant medical care, and single-parent households. We also examine whether the increase in the total FES score from T1 to T2 is clinically significant. However, the clinical minimum significant difference for FES is not clear; therefore, this is discussed through a comparison with a previous study [12].

An intergroup comparison is similarly conducted for the secondary outcomes using the analysis of covariance for each outcome at T2. The results at T1 and T3 for the early group are examined using a paired *t* test to determine whether the intervention effect observed at T2 is sustained. The results at T2 and T3 for the delayed group are examined using a paired *t* test to determine whether the intervention effect observed in the early group is reproduced in the delayed group.

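### The single-group paired t tests at T3 cannot by themselves establish that the effect is sustained or reproduced: T1 vs T3 shows only that scores remain above baseline, and the delayed group's T2 vs T3 ignores its own waiting period

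*Protocol article*

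**What the plan says.** All of this is in the Data analysis section of the protocol article, except where noted.

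- **Controlled comparison.** There is one for each outcome, at T2. For the main efficacy outcome, "The primary analysis is an intergroup comparison using analysis of covariance with the total FES score at T1 as the covariate" and the T2 total as the dependent variable. The secondary outcomes are handled in the same way.
- **Durability.** The section sets out to verify "whether any interventional effect observed at T2 is sustained (each outcome score at T3 for the early group"). The test is named later: "The results at T1 and T3 for the early group are examined using a paired" t test, and its purpose is given as a "test to determine whether the intervention effect observed at T2 is sustained".
- **Replication.** "The results at T2 and T3 for the delayed group are examined using a paired" t test, described as a "test to determine whether the intervention effect observed in the early group is reproduced in the delayed group".
- **Treatment status.** Under Data collection method, the delayed group answers T1 roughly 5 weeks before its program, "T2 immediately before attending the program, and T3 immediately after completing the course". It is therefore untreated from T1 to T2 and treated from T2 to T3.

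No controlled analysis uses T3, and nothing limits what may be concluded from the two paired tests.

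**The concern.** There are two separate faults, one in each test.

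**Durability.** Whether a gain seen at T2 was kept depends on what happened between T2 and T3. The T1 vs T3 test does not use T2. It can be significant after much of the gain has gone, and in a small group it can miss significance when little has been lost. It answers whether the group is still above its starting point, which is a weaker statement than that the T2 effect was kept.

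**Replication.** The T2 vs T3 test in the delayed group attributes the whole change to the program. Time trend, the effect of repeating the questionnaire and regression to the mean are all included in that change. The same people supply an untreated T1-T2 change over a similar interval, and the test does not use it.

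These two tests are the article's only stated basis for statements about durability and replication. A report that follows the plan literally could call an effect sustained after half of it had gone, or reproduced on a change that the waiting period already showed.

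**Working it through.** **Inputs**
- Total N = 52, effect size 0.33, two-sided 5% level assumed (Sample size; Data analysis). The allocation ratio is not stated. I assume 1:1, so n = 26 per group.
- T2 gain: 0.33 read as Cohen's f. With two equal groups d = 2f = 0.66, taken in units of the score SD. This is an assumption, used only to set a scale. N = 52 does not itself reproduce from f = 0.33 at 80% power (the ANCOVA calculation gives 75). That is a separate matter on which nothing here depends.
- Correlation r between any two time points: not in the documents; 0.5 and 0.7 are tried.
- Drift common to both groups: not in the documents; 0.10 to 0.20 SD per 4 weeks is tried.

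**Formulas (SD = 1, equal correlations)**
- SD of a paired difference = sqrt(2(1-r)): 1.000 at r = 0.5 and 0.775 at r = 0.7.
- Noncentrality = (mean change / SD of difference) x sqrt(26). The rejection rate comes from the noncentral t with 25 df.

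**Step 1. T1 vs T3 when part of a real gain is lost (no drift)**

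| Share of 0.66 SD kept at T3 | Net change | r = 0.5 | r = 0.7 |
|---|---|---|---|
| All | 0.66 | 90% | 99% |
| Three quarters | 0.495 | 68% | 88% |
| Half | 0.33 | 37% | 55% |

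For the half-kept row, the noncentrality is 0.33/1.000 x 5.099 = 1.68 at r = 0.5 and 0.33/0.775 x 5.099 = 2.17 at r = 0.7. With 10% dropout (n = 23) that row becomes 33% and 50%.

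**Step 2. Delayed-group T2 vs T3 with no program effect, read alone (two-sided)**

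| Drift per 4 weeks | r = 0.5 | r = 0.7 |
|---|---|---|
| 0.10 SD | 8% | 10% |
| 0.15 SD | 11% | 16% |
| 0.20 SD | 17% | 24% |

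The nominal rate is 5%. Almost all of these rejections are in the favourable direction.

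**Step 3. The same null, but a favourable significant T2 ANCOVA is required first**

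This was simulated with 26 per group, linear drift shared by comparable groups, and drifts of 0.10 and 0.20 SD. The ANCOVA is favourably significant in about 2.5% of trials. The ANCOVA together with early T1 vs T3 is significant in about 0.7-2.3%. The ANCOVA together with delayed T2 vs T3 is significant in about 0.6-1.4%.

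**Step 4. The drift-adjusted contrast in the delayed group**

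(T3-T2) minus (T2-T1) = T3 - 2T2 + T1. Its variance is 1 + 4 + 1 + 2r - 4r - 4r = 6(1-r), so its SD is 1.732 (r = 0.5) or 1.342 (r = 0.7). Steady drift cancels, and the favourable false-positive rate stays at the nominal 2.5%. For a 0.66 SD effect the noncentrality is 1.94 or 2.51, which gives 46% or 67% power. The plain paired test has 90% or 99%. The CI is wider by sqrt(3) = 1.73.

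**The case against.** **Both questions follow on from the T2 result.** The plan asks whether an effect already observed is sustained or reproduced, and T2 has a between-group ANCOVA. A reader might infer that drift alone would often be reported as a lasting effect, because with no program effect, r = 0.7 and drift of 0.15 or 0.20 SD the T1 vs T3 test is significant in 48% or 72% of trials. The documents do not support that reading. Those rates take the paired test in isolation and fall to 31% and 50% at r = 0.5. Once the T2 ANCOVA comes first, false claims under a full null are rare (Step 3). This part of the objection stands. It has two limits: the plan states no formal gate, and a gate does nothing about partial loss of a real effect, which is the case in Step 1.

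**T1 vs T3 is a legitimate question.** Still being above baseline is one ordinary sense of sustained. That is fair, and the test is worth keeping under that name. It does not show that the T2 gain was kept.

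**No untreated group exists at T3.** This is correct. It would be wrong to say that the plan throws away a control for durability, since the waitlist design has none at that point. The T3-T2 change in the early group is just as uncontrolled, and upward drift could hide a loss. Only the replication test leaves usable control information aside.

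**Clinical relevance.** The plan also says "We also examine whether the increase in the total FES score from T1 to T2 is clinically significant", and a reader might infer a third uncontrolled decision rule. The text does not bear this out: the plan states that no minimum important difference is clear and that the point is only discussed against a previous study. The controlled T2 difference comes from the primary efficacy analysis anyway.

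**Scale.** The declared primary outcome is feasibility, these are follow-on analyses, and no design decision is tied to them. That limits the weight of the point but does not remove it, because the article also aims to verify efficacy.

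**Conclusion.** The concern holds in a limited form. The two paired tests are stated rules that can give the wrong answer to the questions they are assigned.

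- **Durability:** T1 vs T3 is significant in 37-55% of trials when half of a 0.66 SD gain has been lost, and in 68-88% when a quarter has. This needs no drift assumption. It rests on n = 26, on 0.33 being Cohen's f, and on r between 0.5 and 0.7.
- **Replication:** read alone, delayed T2 vs T3 is significant in 8-17% (r = 0.5) to 10-24% (r = 0.7) of trials with no program effect, if scores drift by 0.10-0.20 SD per 4 weeks. The drift is assumed, and the documents give no evidence for or against it. After a significant T2 ANCOVA, a false claim under a full null is rare.

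The results can support statements about durability and replication but cannot verify them. The point deserves a change to the analysis text. It does not threaten the primary T2 comparison or the feasibility objective.

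**What to change.** In Data analysis:

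1. **Durability.** Report the early-group T3-T2 change with a 95% CI, beside the controlled T2 between-group effect. Keep T1 vs T3, labelled as showing whether scores are still above baseline. State that no untreated control exists at T3, so drift could mask a loss, and that a non-significant T3-T2 change does not prove maintenance.
2. **Replication.** Report the delayed-group contrast (T3-T2) minus (T2-T1) with a 95% CI, beside the planned paired test. State the assumption that drift is steady over the two intervals.
3. **Wording.** Describe both results as supportive of a T2 effect and drop the claim that they verify durability or replication.

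**Cost.** Only analysis text and a few lines of code change; no new data or visits are needed. The downside is precision: the drift-adjusted contrast has about 46-67% power for a 0.66 SD effect, against 90-99% for the paired test. It should therefore be read through its interval, with the paired test shown alongside.

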### Sample size

The sample size is estimated by selecting *F* tests (ANCOVA) using G*Power software version 3.1.9.7 [14]. The required sample size is calculated based on data obtained from the pretest implemented with the same subjects and equivalent program content as used in this study. The required sample size is 52, assuming an effect size of 0.33, a test power of 80%, and an *α* value of 0.05. The dropout rate is assumed to be 10% based on a previous study with an online program for parents of children with disabilities [15]. From a feasibility study perspective, a formal sample size calculation is not essential. Our sample size calculation is based on the pragmatics of recruitment and the necessity for examining feasibility among a broad group of families caring for children with disabilities.

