The response information is collected in the online survey system. Participants are allocated identity documents (IDs) that are linked to the response information, and every response of each participant from T1 to T3 can be linked. If there are multiple responses from the same person at the same time (duplications), it is assumed that it is because the respondent wished to correct their answer; hence, the later response is adopted. The data collected in the online survey system are backed up fortnightly. Once all the participants complete the follow-up evaluations, the data are downloaded from the system and stored as primary raw data.

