The following two analyses are conducted as a sensitivity analysis of the primary analysis. The first is a re-analysis of the dropouts from T1 to T2 with the amount of change in the total FES score set as 0, to consider the effect of dropouts. The second is a per-protocol analysis. That is, re-analysis is conducted to compare the results of participants who attended all four sessions of the program (group) to all others (group).

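### The per-protocol sensitivity analysis of T2 FES groups by attendance across both arms with no T2 cut-off, so it is not a per-protocol contrast of early with delayed

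*Protocol article*

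**What the plan says.** All references are to the Method section of the protocol article.

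- **Primary endpoint and model (Data analysis).** The article states that "the primary outcome measure is the total FES score at T2", compared between groups by "analysis of covariance with the total FES score at T1 as the covariate, and the total FES score at T2 as the dependent variable". Participants who do not attend as scheduled stay in their original allocation group.
- **Sensitivity analyses (Data analysis).** "The following two analyses are conducted as a sensitivity analysis of the primary analysis". One is a "re-analysis of the dropouts from T1 to T2 with the amount of change in the total FES score set as 0". The other is called per-protocol: "re-analysis is conducted to compare the results of participants who attended all four sessions of the program (group) to all others (group"). Neither an arm nor a date limits who counts as an attender.
- **Timing (Data collection method).** The delayed group completes "T2 immediately before attending the program, and T3 immediately after completing the course". Participants are surveyed whether or not they attend, so early participants with incomplete attendance can supply T2 scores.

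**The concern.** A per-protocol analysis normally keeps the allocated comparison and restricts each arm to those who followed their assigned schedule. For a T2 outcome here, the early arm's schedule is four sessions before T2 and the delayed arm's is none. The stated rule replaces that with attenders against everyone else.

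Two things follow. First, early participants with one to three sessions join the delayed group in the comparator, so the comparator is partly treated. Second, both arms eventually receive the programme. Unless attendance is cut off at T2, delayed participants who go on to complete it meet the definition of attender while contributing a pre-programme score.

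This is the article's only analysis of the effect under full attendance. If it mixes treated and untreated scores on both sides, it can come out well below the primary estimate and look like a failure to confirm it.

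**Working it through.** **The plan's own figures.** The article gives no completion rate and no expected result for this analysis, so there is nothing to reproduce directly. The Sample size section supplies only a setting: "The required sample size is 52, assuming an effect size of 0.33, a test power of 80"%. Read as Cohen's f with one covariate, 0.33 needs N = 75, and N = 52 gives power 0.645. That mismatch is a separate matter. It affects the power figures in step 5 but not the recovered fractions.

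**Assumptions.** Arms are 1:1. The share c attending all four sessions is the same in both arms, unrelated to outcome, and ranges from 0.60 to 0.90. Full attendance changes T2 FES by δ, and incomplete attendance gives qδ with q = 0 or 0.5. No delayed participant has had a session at T2.

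**1. Literal reading (attendance at any time).**
- Attenders are a share c of each arm. Half carry δ and half carry 0, so the mean effect is δ/2.
- All others are a share 1 − c of each arm. Half carry qδ and half carry 0, so the mean effect is qδ/2.
- Contrast = δ/2 − qδ/2 = 0.5(1 − q)δ, whatever c is.
- q = 0 gives 0.50δ; q = 0.5 gives 0.25δ.

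**2. Attendance counted up to T2.**
- Attenders are early completers only, with mean effect δ.
- All others are the whole delayed arm (weight 1, effect 0) plus early non-completers (weight 1 − c, effect qδ), with mean qδ(1 − c)/(2 − c).
- Contrast = δ[1 − q(1 − c)/(2 − c)].
- q = 0 gives 1.00δ.
- q = 0.5, c = 0.60: 1 − 0.5 × 0.40/1.40 = 0.857.
- q = 0.5, c = 0.80: 1 − 0.5 × 0.20/1.20 = 0.917.
- q = 0.5, c = 0.90: 1 − 0.5 × 0.10/1.10 = 0.955.

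**3. Within-arm definition.** Early completers against delayed participants gives δ − 0 = δ. This holds because completion was assumed unrelated to outcome, which real attendance may not be.

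**4. Against the allocated comparison.** The primary contrast expects δ[c + (1 − c)q].

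| q | Primary, c = 0.60 to 0.90 | Literal | Counted by T2 |
|---|---|---|---|
| 0 | 60% to 90% | 50% | 100% |
| 0.5 | 80% to 95% | 25% | 86% to 95% |

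On the literal reading the check falls below the analysis it is meant to support in every row. Counted by T2, it does not.

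**5. Power.** For two equal groups f = 0.33 is d = 2 × 0.33 = 0.66 residual SD. ANCOVA was simulated with 26 per arm and an assumed T1–T2 correlation of 0.7, over c = 0.60 to 0.90.
- Literal contrast: expected difference 0.5 × 0.66 = 0.33 SD (q = 0) or 0.25 × 0.66 = 0.165 SD (q = 0.5), with power about 0.055 to 0.19.
- Within-arm contrast: about 0.66 SD, with power about 0.50 to 0.61.

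**The case against.** The best defence is that the rule should be read in context. It belongs to an analysis of T2, and the article itself places the delayed group's T2 before its programme, so attendance that matters for T2 is attendance by T2. A reader might infer that untreated delayed completers will certainly be classed as treated. The documents do not establish that. The line "Once all the participants complete the follow-up evaluations, the data are downloaded from the system" concerns survey responses; it shows that analysis follows all follow-up, not which attendance window applies. On the contextual reading the loss is at most about 14% over the range tested, towards the null. This stands, and it limits the size of the point. It does not remove it: the sentence names no cut-off, two readings give very different answers, and on both of them partly treated early participants sit with the controls.

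Three further inferences also go too far.

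- **That the primary result is compromised.** It is not. It follows original allocation, and feasibility, assessed descriptively, is the study's stated primary outcome.
- **That setting dropouts' change to zero is an error.** It is a simple, conservative check. In simulation at N = 52 and the planned 10% dropout, the estimate shrank by about 10%. The standard error was 0.268 to 0.272 residual SD, against 0.279 with no dropout. Coverage was about 94% and type I error near 5%, under random dropout with no time trend.
- **That allocation could serve as an instrument for a complier-average effect.** Allocation follows application order and is not randomized, so the documents give no basis for treating it as one.

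**Conclusion.** The point holds as a fault in a stated rule, at minor to moderate severity. The analysis called per-protocol is an attendance grouping across arms: it mixes partly treated with untreated participants on either reading, and on the literal one it also counts untreated delayed completers as treated. The literal contrast keeps only 25% to 50% of the full-attendance effect for q between 0.5 and 0, and counting attendance by T2 keeps about 86% to 100%. These fractions rest on 1:1 arms, equal completion of 60% to 90% unrelated to outcome, and at most half benefit from incomplete attendance, none of which the article states. The large loss therefore depends on the literal reading; the mixing of arms does not.

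**What to change.** Replace the sentence with a definition within arms: early participants who attended all four sessions by T2, compared with delayed participants who have a valid T2 given before their first session. Use the primary ANCOVA with T1 FES and baseline covariates, and state that attendance is self-selected, so the result supports the primary analysis and does not replace it. If the attendance grouping is kept, state that attendance is counted up to T2 and call it as-treated.

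The cost is a few lines of text and code and no new data. The downside is that early non-completers leave this set: 0.20 × 26 ≈ 5 of 26 if 80% complete, and between 0.10 × 26 ≈ 3 and 0.40 × 26 ≈ 10 over the range above. Selection bias from comparing self-selected completers with the delayed arm remains.

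The zero-change analysis can stay. Multiple imputation could be added as a supplement; if it uses T3, it must treat the arms separately, because the delayed group's T3 follows its programme.
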